### 2.5. Process Evaluation

#### Effective Elements

During the entire project, we will gather data on the process of developing a collective prevention project to determine effective elements. This will be achieved in regular meetings between researcher and co-researchers. These informal conversations are designed to keep track of each team’s progress and to ask the co-researchers about breakthroughs, questions or possible issues they encounter in their project. This provides input for topics or information that are addressed in webinars with the larger group of participating DN. These webinars will take place once per two months in the first year, and approximately once per three months in the following years. Furthermore, the researcher will visit relevant events or activities of the prevention projects, such as walking groups, workshops or other gatherings, to gather observational data in the form of notes. Lastly, annual focus groups will be held with DN based on a semi-structured topic list (see Supplementary Materials, Topic list S3). This list consists of the following topics: views on prevention, collaboration with and involvement of community members, process of organising a prevention project and the support that teams receive in this process.

### 2.6. Analyses

#### 2.6.1. Quantitative Analyses

For the quantitative analysis we measure three dependent variables (quality of life, experienced health and social participation) in all of the 14 prevention programmes once a year. We estimate that 25–30 community members will be involved per locality, resulting in a sample size of 350–420 individuals. All variables will be analysed descriptively per year. We will use a repeated measures MANOVA to assess the change within subjects for the dependent variables over time (4 time points). We will use the same test to make between-group comparisons of the individual prevention programmes if the sample size allows this.

Quantitative project specific measures will most likely have an inadequate sample size for a solid quantitative analysis, so these will only be analysed descriptively. In case of multiple teams using the same project specific measure (e.g., Lubben Social Network Scale), we may be able to make comparisons in change of these variables over time and between the different projects. As Buurtzorg teams will determine the design of their project depending on the findings in phase 1, we cannot determine this in advance.

Job satisfaction will be analysed descriptively every year. The change over the years (4 measurement times) will be compared within subjects using a repeated measures ANOVA. We will also conduct a t-test to compare the change in job satisfaction for participating DN with the larger group of Buurtzorg DN who do not participate in the study but answer the same questions as part of the standard annual Buurtzorg questionnaire. The same analysis will be performed on the mean hours of care per client per Buurtzorg team, except in this case each data point represents a team instead of an individual.

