## 2. Materials and Methods

### 2.1. Population

The study population in this Collective Prevention project will consist of two groups: DN and community members. The DN are all employees of community healthcare organisation Buurtzorg. Buurtzorg has created a model of care in which self-managing teams of 6–12 nurses deliver all the care that a patient needs. They help people get ready in the morning, wash them, give medication, but also provide medical care such as wound treatment. The teams try to involve the formal and informal networks of their patients to sustain independency for as long as possible. The teams organize their work together and share the workload and responsibility for the quality of care. Buurtzorg has invited all interested teams to apply for the current project by submitting their motivations to work on prevention in their work area. The whole team needs to be on board with the project and they are made aware that they will spend roughly 8 hours a week on the project. The motivations and capabilities of the teams were assessed during an interview. At the time of writing, 18 Buurtzorg teams, from 14 different localities all over the country, are selected to participate. These localities vary in number of inhabitants (1230–19,400), mean income (€26,000–€40,000) and urbanity (1–5) on a scale from 1 (most urban: >2500 addresses per km^2^) to 5 (least urban: <500 addresses per km^2^) [42]. The target population of the collective prevention projects consists of the 55+ population in the neighbourhoods under study. The only strict inclusion criterium for this study is that the participants live in one of the neighbourhoods under study and participate in the project in the neighbourhood on a regular basis. DN will be responsible for recruitment of this study population through interviews and networking in their locality, for which they will receive training and tips during workshops led by the researchers. Participation in both the prevention project and this study is voluntary and, therefore, we work with a convenience sample. Given the range of localities we aim for a diverse population in terms of sex, civil status and income. We expect to involve approximately 25–30 community members per site, amounting to a total of 350–420 individuals in our community sample.

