### 3.2. Limitations

This study will take place in 14 different localities with prevention projects that are designed for that specific context. This makes the projects relevant for the neighbourhood, but also comes with challenges in generalisability and comparing the prevention projects and their health and social effects. For example, the effects could be different for different ethnic groups due to underlying differences in views and perceptions regarding health, social norms and collective prevention. This should be taken into account if prevention projects are deployed in more localities. Additionally, the participating Buurtzorg teams are not selected at random, but they apply for participation in the project and are selected based on a strong motivation and willingness to work on prevention. This means that the sample of district nurses in this project likely already has a certain set of characteristics or values that are different from a randomized sample. It should, therefore, be noted that the implementation of collective prevention programmes in all Buurtzorg teams may shine light on new challenges or required skills and knowledge that may have been taken for granted in the selected sample of the current study. Furthermore, it is difficult to accurately measure prevention, as the desired outcome is a non-event. In addition, there is no control group in this study and we can only compare with general population outcomes. Furthermore, we are not able to control for the effect of planning and organizing a project in a community. Structural Governance and Collective Empowerment are two practices in community-based participatory research that influence the outcomes through interaction with the context, relationships and other aspects of the research [52]. This means that the health and social effects that we will measure cannot only be attributed to the content of the prevention project. Finally, results in this study will mainly be based on a population of relatively older people, since they are more likely to have the time to help organise such a project. Whereas collective prevention should be focused on all ages, as this is the best way to collectively change our lifestyle and prevent age-related diseases. This may be a next step for spreading the prevention projects of this study.

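### The repeated measures MANOVA makes no allowance for people being nested in 14 localities, so its test of change over time is anti-conservative to a degree set by an unstated correlation

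*Protocol article*

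**What the plan says.** Section 2.6.1 measures quality of life, experienced health and social participation "in all of the 14 prevention programmes once a year". The method is fixed there: "We will use a repeated measures MANOVA to assess the change within subjects for the dependent variables over time", with four time points. The following sentence lets the same test compare individual programmes, but only if numbers permit. No locality random effect, cluster-robust variance, design effect or ICC is mentioned.

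The structure of the sample is clear. Section 2.1 reports "18 Buurtzorg teams, from 14 different localities all over the country, are selected to participate". Section 2.6.1 gives its size: "We estimate that 25–30 community members will be involved per locality, resulting in a sample size of 350–420 individuals". Section 3.2 adds: "This study will take place in 14 different localities with prevention projects that are designed for that specific context".

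For care hours per client, section 2.6.1 does take the team as the data point. The unit of analysis was therefore considered there, but not for community members.

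**The concern.** A within-subject test removes stable differences in level between localities. It does not remove differences between localities in how much people change. If change varies by locality, two people from one site carry less information about the average change than two people from different sites, and a person-level test understates the standard error.

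The article gives reasons to expect such variation:

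- Each locality designs its own project (2.2, 3.2).
- Delays are expected to differ between teams, so sites will be at different stages in the same measurement year (2.2).
- The intended mechanism is a shared local social network (3.1).
- The variety of the 14 locations is valued because it allows health effects to be compared between contexts (section 3).

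At stake is the only inferential test for the community outcomes, which serve the first primary objective. Section 3.1 also hopes to carry the lessons to all 950 Buurtzorg teams. For that use, the relevant uncertainty includes variation between localities.

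**Working it through.** **Inputs from the protocol article.** 14 localities and 25–30 people in each (2.1, 2.6.1); three outcomes at four time points (2.6.1).

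**The plan's own figure.** 14 × 25 = 350 and 14 × 30 = 420, as stated. This is an expected head count. The article attaches no power calculation to it.

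**Assumption.** The ICC of within-person change (the share of variance in change that lies between localities) is not in the article. It is varied below from 0 to 0.10.

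**Single contrast.** With m people per locality:

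- design effect DE = 1 + (m − 1) × ICC
- effective N = 14m / DE
- true two-sided error of a nominal 5% test = 2 × [1 − Φ(1.96 / √DE)]

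Example at ICC 0.05:

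- m = 25: DE = 1 + 24 × 0.05 = 2.20; effective N = 350 / 2.20 = 159; error = 2 × [1 − Φ(1.96 / 1.483)] = 18.6%.
- m = 30: DE = 1 + 29 × 0.05 = 2.45; effective N = 420 / 2.45 = 171; error = 2 × [1 − Φ(1.96 / 1.565)] = 21.1%.

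| Assumed ICC of change | Design effect | Effective N | True error of nominal 5% test |
|---|---|---|---|
| 0 | 1 | 350–420 | 5% |
| 0.01 | 1.24–1.29 | 282–326 | 7.8–8.4% |
| 0.02 | 1.48–1.58 | 237–266 | 10.7–11.9% |
| 0.05 | 2.20–2.45 | 159–171 | 18.6–21.1% |
| 0.10 | 3.40–3.90 | 103–108 | 29–32% |

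**Joint test.** Three outcomes × (4 − 1) time contrasts = 9 contrasts. Hotelling's T² was simulated with 14 equal clusters, no average change, the same ICC on every contrast and independent contrasts (4,000 replicates). It rejected in about 5% of runs at ICC 0, 13–17% at 0.01, 24–29% at 0.02 and 57–65% at 0.05.

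These joint figures depend on the assumed correlation structure. Further runs at ICC 0.05 (6,000 replicates, person-level correlation 0.4 between contrasts) show how much:

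| Structure of locality effects | Rejection rate |
|---|---|
| Correlation 0.9 between contrasts | 22–27% |
| ICC 0.05 on only three of the nine contrasts | 28–32% |
| Correlation 0 between contrasts | 71–79% |

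The range at ICC 0.05 is therefore about 22–79%. The figures at 0.01 and 0.02 rest on one structure only and would also move with it.

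**Does the optional programme factor help?** Locality was added as a fixed factor in the independent-contrast simulation at ICC 0.05. The overall time test rejected in 60–67% of runs with it, against 57–65% without it. It gives no protection when the target extends beyond these 14 sites.

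**The case against.** The strongest reply has four parts.

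1. **Size.** A reader might infer that the p-values are bound to be far too small. The article does not support this. Everything depends on the ICC of change. An ICC of level, as seen in a cross-sectional survey, is not the relevant quantity, because stable differences cancel. At ICC 0 there is no inflation, and at 0.01 a single contrast is only mildly affected. This stands.

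2. **Target.** The teams applied and were selected, so the localities are not a random sample. If the 14 projects together changed outcomes, a significant result is right for those 14. The hope for 950 teams concerns lessons learned and is not tied to the MANOVA result. Section 2.2 describes the quantitative measures as indicative, and section 3.2 concedes limited generalisability and no control group. This lowers the severity. It does not make the test valid for wider inference, and section 3.2 does not warn of correlation within localities.

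3. **Programme as a factor.** The article foresees comparisons between programmes. That serves statements about differences among these sites, but it is conditional and leaves the overall time test unprotected.

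4. **Condensed article.** Analysis detail may sit in a fuller document. Here, however, the article names the test itself, so the point concerns a stated choice and not an omitted detail.

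A reader might also infer that published confidence intervals will be too narrow. The article announces no intervals, so the point is confined to the test.

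**Conclusion.** The point holds in a bounded form. The named test has no provision for nesting in 14 localities and is anti-conservative, for inference beyond these sites, whenever change varies by locality. The article's own rationale makes that likely, but it gives no figure from which to size it.

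Under an assumed ICC of change of 0.01 to 0.05, a nominal 5% single-contrast test has a true error of about 8% to 21%. The joint test is more fragile in most of the settings simulated. With strongly correlated locality effects it is only slightly worse than a single contrast, so no one joint figure should be quoted as the size of the problem. These results assume equal cluster sizes and complete data.

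Severity: should-fix. The study is uncontrolled, uses a convenience sample and treats its quantitative results as indicative. Correcting the standard error would not settle attribution.

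**What to change.** In 2.6.1, replace the MANOVA by one of two analyses for each outcome:

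- a linear mixed model with time as a categorical fixed effect, an unstructured within-person covariance over the four waves, random locality and locality-by-time effects, and Kenward-Roger or Satterthwaite degrees of freedom; or
- an analysis of the 14 locality mean changes, which is simpler.

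The unstructured covariance matters. Participant random intercepts alone would impose equal correlation over the waves, which is more restrictive than the MANOVA being replaced.

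Also define the clustering unit, since 18 teams work in 14 localities; report the ICC of change; state how multiplicity over the three outcomes is handled once the joint test is dropped; and say that the effective sample size may be below 350–420.

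The cost is a paragraph of wording and standard software, with no change to recruitment or data collection. The statistical price is wider uncertainty. With 13 degrees of freedom, an interval for mean change would be about 1.10 times as wide as the person-level one at ICC 0, and 1.63–1.72 times at ICC 0.05 (√DE × t with 13 df ÷ t with 14m − 1 df).

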#### 2.4.2. District Nurses

##### Job Satisfaction and Motivation

The impact on job satisfaction of the DN will be evaluated using a selection of 17 out of 77 questions from the standard annual Buurtzorg job satisfaction questionnaire (see Supplementary Materials, Questionnaire S2). This selection contains the questions that are most relevant to job satisfaction in relation to this project. The DN of the participating Buurtzorg teams who have a key role in the development of the prevention project will complete this questionnaire once every year. We will also obtain mean scores on these 17 items of Buurtzorg employees who do not participate in the study. This will provide us with a control measure, so we can compare the change over the course of this study between the involved nurses in our programme and those involved in regular care of Buurtzorg. Similarly, we will collect data that Buurtzorg has on mean hours of care per client to track the changes during our project and compare the participating teams with regular teams.

The researchers will conduct individual semi-structured interviews in the first and last year of the project to gather information about DN’s views on preventive care, their motivations to work on prevention, the relation to community care and their view on the prevention project in their team. We will ask questions such as “How does prevention fit into the work of DN according to you?”, “How was the subject of prevention represented in your education and how does this relate to your current view on prevention?”, “Can you name some positive and some less positive aspects of your team’s collective prevention project?” (see Supplementary Materials, Topic list S2). These interviews will be followed by focus groups with each Buurtzorg team with a topic list that transpires from the outcomes of the individual interviews. Topics that are likely to be discussed are different views on prevention, representation of prevention in education, roles in and views on the Collective Prevention programme and collaboration within the team. Prior to these interviews, we obtained informed consent from the DN.

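### The job-satisfaction t-test needs a variance that the described control data do not supply and ignores teams; mean hours per client also needs totals beside it

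*Protocol article*

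**What the plan says.** Section 2.6.1 plans the staff comparison in one sentence: "We will also conduct a t-test to compare the change in job satisfaction for participating DN with the larger group of Buurtzorg DN", the comparison group being nurses "who do not participate in the study but answer the same questions as part of the standard annual Buurtzorg questionnaire".

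Section 2.4.2 says what data each side will supply. In participating teams, the respondents are those nurses "who have a key role in the development of the prevention project will complete this questionnaire once every year". For the other side: "We will also obtain mean scores on these 17 items of Buurtzorg employees who do not participate in the study". It mentions no standard deviation, number of respondents or link between years.

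For hours of care, Section 2.6.1 says: "The same analysis will be performed on the mean hours of care per client per Buurtzorg team". A qualifier in the same sentence makes the team the unit for hours, which leaves the individual nurse as the unit for job satisfaction.

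On selection, Section 2.1 requires: "The whole team needs to be on board with the project". Section 3.2 says of the teams that "they apply for participation in the project and are selected based on a strong motivation and willingness to work on prevention", and treats this as a caution about extending the programme to other teams. Section 2.1 gives 18 participating teams and a team size of 6 to 12 nurses. Section 3.1 gives 950 teams in total.

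**The concern.** There are four linked problems.

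- **Data and test do not match.** A two-sample t-test on change needs a mean change, its variance and a count in each group. If the control side arrives as yearly group means, only a difference between two means is available, taken over whoever answered in each year.
- **Teams are ignored for job satisfaction.** Nurses in one self-managing team share workload, colleagues and project, so their changes are probably correlated.
- **The contrast is selected twice.** Teams were chosen for motivation, and within them only key-role nurses are measured. Section 3.2 addresses the first step only as a limit on wider implementation and does not address the second. The article also does not say whether the other members of participating teams count as controls, although the whole team takes on the project.
- **Mean hours per client depends on who remains a client.** If prevention removes low-need people from care, the mean can move against the true change in total care.

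The staff comparisons are the only ones in Section 2.6.1 with a concurrent comparison group outside the programme, so their validity deserves care.

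**Working it through.** The article gives no sample size, SD, ICC or effect size for job satisfaction, so there is no stated figure to reproduce.

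**Inputs from the article:** 18 participating teams; 6 to 12 nurses per team; 950 teams in all, hence 950 − 18 = 932 others, or 932 × 6 = 5,592 to 932 × 12 = 11,184 nurses.

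**Assumed:** two-sided 5% level; equal SDs in both groups; *m* key nurses per team; team ICC of the change score 0.10 to 0.20.

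**1. What the missing control variance costs.** With group means only, one can still run a one-sample t-test of participants' change against the control change taken as fixed. The ratio of the two-sample to the one-sample standard error is √(1/n₁ + 1/n₀) / √(1/n₁).
- n₁ = 18, n₀ = 11,184: 1.0008.
- n₁ = 216, n₀ = 5,592: 1.0191.

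Treating the control mean as fixed therefore understates the standard error by about 0.1 to 1.9%. The mismatch is one of specification; its numerical effect is small.

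**2. Clustering.** Design effect DE = 1 + (m − 1) × ICC; true error = 2 × [1 − Φ(1.96/√DE)]. This covers the participating side, which dominates the variance.

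| m | ICC 0.10: DE, error | ICC 0.20: DE, error |
|---|---|---|
| 1 | 1.0, 5.0% | 1.0, 5.0% |
| 2 | 1.1, 6.2% | 1.2, 7.4% |
| 3 | 1.2, 7.4% | 1.4, 9.8% |
| 4 | 1.3, 8.6% | 1.6, 12.1% |

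A simulation (18 against 932 teams, 9 nurses per control team, 2,000 runs per setting) agrees. At m = 4 and ICC 0.10, the individual-level Welch test rejects in 8.8% of null runs and the one-sample test in 8.95%. A Welch test on team means rejects in 4.2 to 5.6% across all settings run.

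**3. Colleagues counted as controls.** With one key nurse per team, the remaining members number 18 × 5 = 90 to 18 × 11 = 198. If counted as controls they would be 90/(5,592 + 90) = 1.6% to 198/(11,184 + 198) = 1.7% of that group. The dilution is slight, but the group should be defined.

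**4. Hours per client (invented illustration).** Take 20 clients at 1 h and 30 at 5 h: total 20 + 150 = 170 h, mean 170/50 = 3.4 h. If 10 low-need clients no longer need care, the total is 10 + 150 = 160 h and the mean is 160/40 = 4.0 h. The mean rises 18% while total care falls 6%. Section 3.1 hopes for this kind of change: more people managing with little or no nursing help.

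**The case against.** The phrase about mean scores may mean each employee's average over the 17 items. Section 2.6.1 supports that reading, since it contrasts team data points for hours with individual ones for job satisfaction. The article is also condensed, and the extract format may be settled elsewhere. This stands as a possible reading, but the text does not settle it. A reader might infer that the test cannot be run at all. The documents do not support that: individual data may be intended, and even with group means a one-sample test is feasible and nearly equivalent.

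The clustering problem may be absent. Section 2.2 has each team choose one co-researcher, and the note to Figure 1 describes co-researchers in terms close to those used for key-role nurses. If they are the same people, there is one per team and no inflation on the participating side. The wording is not identical, so this remains open. A reader might also apply full team sizes of 6 to 12 and obtain errors of 11 to 27%. That would describe an individual-level test on whole teams, which is not planned.

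Measuring involved nurses is a deliberate choice, and analysing change removes stable baseline differences. Both points stand. Neither removes the possibility that motivated nurses change differently from others.

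Hours per client can properly capture fewer care tasks for people who remain clients. That is a reason to keep the mean, with the totals beside it.

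**Conclusion.** The point holds in moderate form. The control data as described do not supply the variance the planned test needs, and Sections 2.4.2 and 2.6.1 must be reconciled. The numerical cost of treating the control mean as fixed is small, at most about 1.9% of the standard error with equal SDs.

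Ignoring teams raises the type I error to about 6 to 10% with two or three key nurses per team, and not at all with one. This rests on an assumed ICC of 0.10 to 0.20 and on a number of key nurses that the article does not give. The bias from selecting key nurses cannot be quantified from the article. The hours measure can move against total care, as the illustration shows, but how often it would is unknown.

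A reader might infer that survey data on every member of the participating teams are already to hand. The article says only that the questionnaire is a standard annual one. It does not say that all members of those teams answer it, that answers can be linked to teams or years, or that the researchers may have them.

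Section 3 does not list job satisfaction among the primary objectives, so no primary conclusion depends on this test. The correction is worth making but is not essential to the study.

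**What to change.** - State in Sections 2.4.2 and 2.6.1 the form of the control data and the number of key-role nurses per team.
- Request from the standard annual questionnaire, for each year, team-level means, SDs and respondent counts, or individual records with a team identifier.
- Compare change between participating and non-participating teams with the team as unit, or with team-clustered standard errors.
- Exclude the other members of participating teams from the control group. Keep the key-nurse comparison as stated, and add a whole-team comparison if those responses can be obtained.
- Analyse total hours of care and number of clients per team alongside mean hours per client.

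The cost is a somewhat larger extract from the annual questionnaire and from Buurtzorg's hours-of-care data, whose availability must be confirmed first. A whole-team comparison would dilute an effect confined to key nurses, which is why both should be reported. Self-selection of teams remains, so the result should still be described as a non-causal comparison.
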